### Ethical considerations

The study has been structured in accordance with the Helsinki Declaration [41] and approved by the University of Malawi College of Medicine Research and Ethics Committee and Washington University School of Medicine Human Research Protection Office. Consent for conducting the study was obtained from district health officials and community leaders. Prior to enrollment, large-group community meetings will be held to inform potential participants, their caregivers, and any interested members of the community about the study and answer their concerns. Consent from all caregivers will be obtained in written and verbal forms by native Chichewa-speaking Malawian research nurses, and those who cannot sign their names will submit thumbprints instead (Additional file 2).

Given that the intervention proteins are a normal component of breast milk, it is extremely unlikely that any adverse effects will be observed. No specific data safety monitoring committee will be used, but rather daily monitoring for any adverse events will be conducted by the field staff and reviewed and investigated by the study principal investigators. Additionally, at each follow-up visit caretakers will be specifically queried about the presence of any ill symptoms or unusual clinical events in their children in an attempt to proactively identify any untoward effects.

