### Outcomes and sample size

The primary outcomes of interest will be improvement of a major biomarker of EED, the percent of ingested lactulose excreted in the urine (Δ%L), from baseline to 8 weeks and to 16 weeks. Linear growth has been shown to best correlate with this component of the traditional dual-sugar absorption test [42]. The enrollment goal will be at least 86 subjects in each of two equally sized intervention or control groups. This sample size was chosen to detect a decrease of 0.05% in Δ%L between the two groups (considered to be a clinically significant improvement in gut barrier function) with an alpha value of 5% and 90% power. This assumes that urinary lactulose measurements will be distributed similarly to prior studies that showed that more than 80% of apparently healthy rural Malawian children had EED. Additional children will be enrolled to account for children who drop out or are excluded during the course of the study, as well as for some children who will not have a satisfactory data collection due to technical issues with the urine collection. The differences in lactulose recovery before and after the intervention will be calculated and compared between the intervention and control groups using *t* tests if the data are normally distributed or the non-parametric Wilcoxon Rank Sum Test if the data are not normally distributed.

Secondary outcomes of interest include linear and ponderal growth, adverse gastrointestinal symptoms, and any side effects due to the interventions. Linear growth will be calculated as the change in length over time, expressed as mm/day. Weight change will be calculated as the change in weight over time, normalized to the enrollment weight, and expressed as g/kg/day. Exploratory analyses of mRNA markers of intestinal inflammation found in the stool will also be conducted as part of our ongoing investigations into identifying novel biomarkers for EED [43, 44].

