### Study participation

On the enrollment date, children will be screened for eligibility via clinical anthropometric measurements and a short questionnaire regarding recent illnesses. Children without any exclusion criteria will be given a study number, and will complete the lactulose absorption test, stool collection, and blood draw after consent is provided. HSAs will work with caregivers to complete a questionnaire that includes basic sociodemographic, economic, sanitary, and dietary data specific to lactoferrin- and lysozyme-containing foods, along with an account of recent illnesses in the previous 7 days. After completion of sample collection, each participant will receive a 4-week supply of the intervention corresponding to their assigned study number. Local staff will then educate caregivers on how to prepare and feed the interventions to the children. Recruitment of trial participants began in October 2016 and the trial is ongoing.

At subsequent monthly visits, study participants will return for anthropometric measurements, with or without sample collections. Questionnaires that primarily detail recent illnesses, medical visits, diet, and compliance by asking the caretaker how many days of the intervention were missed will be completed. The complete schedule of study visits, testing, and distribution of interventions is provided in the SPIRIT format in Fig. 2.

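### Outside the gut, an event enters the named safety outcome only if it is judged caused by the product; count all reported events by arm instead

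*Protocol article*

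**What the plan says.** The Protocol article describes the collection of safety information in one place and the safety outcomes in another.

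- **Collection (Ethical considerations).** No separate safety committee is used. Instead, "daily monitoring for any adverse events will be conducted by the field staff and reviewed and investigated by the study principal investigators". A second source follows: "at each follow-up visit caretakers will be specifically queried about the presence of any ill symptoms or unusual clinical events in their children". Neither source is limited to events thought to be related to the product. The same section states that "it is extremely unlikely that any adverse effects will be observed".
- **Outcomes (Outcomes and sample size).** Besides growth, the secondary outcomes are "adverse gastrointestinal symptoms, and any side effects due to the interventions".
- **Contacts (Study participation).** "At subsequent monthly visits, study participants will return for anthropometric measurements, with or without sample collections". At enrolment "each participant will receive a 4-week supply of the intervention corresponding to their assigned study number". The follow-up forms are described as "Questionnaires that primarily detail recent illnesses, medical visits, diet, and compliance by asking the caretaker how many days of the intervention were missed".
- **Analysis (Data management and analysis).** Fisher's exact test is the general choice for discrete variables and Student's t test for continuous ones, at the 5% level. The section extends these methods to all the clinical data.

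**The concern.** The outcome is narrower than the collection. Staff gather events of every kind, but outside the gut the named outcome is restricted to effects caused by the intervention. Someone must therefore rule on causality, event by event, before an event counts.

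A randomised comparison does not need that step. Background illness falls on both arms alike, and any excess in the active arm shows in the all-cause counts. With individual attribution, the result depends on the judgement and its expectations. Here the only stated reviewers are the principal investigators, and the article already regards adverse effects as very improbable. An expectation of that kind tends to lower the number of events accepted as causal. The trial could then report few or no side effects although reported events differed between arms.

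Events outside the gut are conceivable for this product. The active arm receives bovine lactoferrin (Intervention groups), and dairy allergy is an exclusion criterion (Eligibility criteria), so the plan itself recognises one possible reaction that need not be gastrointestinal.

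**Working it through.** The plan states no figure for the safety outcomes, so there is none to reproduce. The check compares the passages and then follows what the causal filter does.

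**Step 1. Collection against outcome.**

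| Type of event | Collected? (Ethical considerations) | Enters a named outcome? (Outcomes and sample size) |
|---|---|---|
| Gastrointestinal symptom | Yes, any cause | Yes, no causal judgement required |
| Any other adverse event | Yes, any cause | Only if judged due to the intervention |

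The mismatch is confined to the second row.

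**Step 2. Effect of the filter.** Let p_T and p_C be the true risks of a non-gastrointestinal event per child in the active and control arms, with at most one event per child for simplicity. Let a, between 0 and 1, be the share of events judged causal. Assume that a is the same in both arms, as it would be if reviewers judge without knowing the arm.

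- True risk difference: p_T − p_C.
- Counted risk difference: a·p_T − a·p_C = a·(p_T − p_C).

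The counted difference is never larger than the true one, and it goes to zero as a does. The documents give neither p_T, p_C nor a, so the factor can be anything from 0 (all signal lost) to 1 (none lost).

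**Step 3. What a zero count would mean.** The enrolment goal is 86 children per arm. With no counted events among 86, the exact one-sided 95% upper limit on the counted risk is 1 − 0.05^(1/86) = 0.034, or 3.4%. This limit applies to a·p_T. The corresponding limit for the true risk p_T is 3.4%/a, which equals 3.4% only when a = 1 and loosens as fewer events are accepted as causal. A zero on an all-cause count needs no such division.

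**Step 4. The stated monitoring against the described contacts.** Treatment lasts 16 weeks, 16 × 7 = 112 days. Monthly visits with a 4-week supply give four contacts after enrolment, one per 112/4 = 28 days. The text names no route by which events are gathered between them. That leaves the daily monitoring unexplained, but not contradicted: staff can receive and review reports every day without seeing each child every day.

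**The case against.** Much can be said for the plan, and most of it stands.

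- **Not everything is filtered.** A reader might infer that the trial counts only events attributed to the product. It does not. Gastrointestinal symptoms are a separate secondary outcome with no attribution, and they are the most relevant events for an oral gut product.
- **Safety is measured.** A reader might infer that safety rests on daily monitoring alone and would be reported without having been measured. The all-cause caretaker query at every follow-up visit rules that out.
- **Daily monitoring is not shown to be missing.** The complete visit schedule is in Fig. 2, which is not reproduced in the text at hand, and an article may leave procedures between visits to the full protocol. Children also live within walking distance of the clinic site, so reports could be brought there at any time.
- **Recall is not shown to be short.** The only window given is at enrolment: "along with an account of recent illnesses in the previous 7 days". Carried to follow-up, which is an assumption, it would cover 7/28 = 25% of each interval. If recall runs back to the previous visit, coverage is 100%. The article does not say which, so neither figure demonstrates a defect.
- **A comparison by arm is already possible.** Events of any cause are collected, and the tests named in Data management and analysis apply to all clinical data. Nothing prevents an all-cause table.
- **Attribution can help.** A reviewer who could separate product effects from background illness would remove noise. That investigators' expectations will lower the count is a risk, not a demonstrated fact.

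The last two arguments do not remove the point. That an all-cause comparison is possible does not make it the named outcome, and the benefit of attribution depends on a judgement whose accuracy the trial cannot check.

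**Conclusion.** The point holds as a matter of outcome definition. As worded, non-gastrointestinal events enter the named outcome only after a causal judgement, although the trial collects them whatever their cause. This could mask a real difference between arms. The size cannot be fixed from the documents: under equal attribution in both arms, the observed difference is the true one multiplied by an unknown factor between 0 and 1. The conclusion assumes that the outcome will be applied as written, with the stated reviewers doing the attribution.

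It does not extend further. The documents do not support a claim that daily monitoring is absent, that gastrointestinal symptoms are under-counted, or that safety goes unmeasured. How events are captured between visits is a minor clarification. The primary outcome and the sample size are unaffected.

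**What to change.** 1. **Outcomes and sample size.** Define the safety outcome as all reported adverse events and gastrointestinal symptoms, whatever their judged cause. Count them per child, as the number of children with at least one event, and compare randomised arms with Fisher's exact test, as Data management and analysis already provides. Report the investigators' causality judgement descriptively only.
2. **Ethical considerations and Study participation (minor).** Reconcile the daily monitoring with the monthly contacts by saying how events are captured between visits. State the recall period used at follow-up in the same place.

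The cost is a few lines of wording. The data are already to be collected, and no visit, sample or child is added. The small downside is that more background illness will be tabulated, so the tables will be longer and will contain more events unrelated to the product.

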### Eligibility criteria

All children within the enrollment ages of 12 to 23 months of age who live within walking distance of the Mmwenye village clinic site will be screened for eligibility. Participants will be excluded if the child cannot drink 20 mL of sugar water or otherwise give the necessary biological samples, or if the family plans to move from the area during the study duration. Children will also be excluded if they are moderately or severely malnourished (defined as having a weight-for-height *Z* score < –2, mid-upper arm circumference (MUAC) < 12.5 cm, or presence of pitting edema), have congenital disorders or chronic diseases, dairy allergy, or have acute illnesses such as fever, cough, or diarrhea.

### Outcomes and sample size

The primary outcomes of interest will be improvement of a major biomarker of EED, the percent of ingested lactulose excreted in the urine (Δ%L), from baseline to 8 weeks and to 16 weeks. Linear growth has been shown to best correlate with this component of the traditional dual-sugar absorption test [42]. The enrollment goal will be at least 86 subjects in each of two equally sized intervention or control groups. This sample size was chosen to detect a decrease of 0.05% in Δ%L between the two groups (considered to be a clinically significant improvement in gut barrier function) with an alpha value of 5% and 90% power. This assumes that urinary lactulose measurements will be distributed similarly to prior studies that showed that more than 80% of apparently healthy rural Malawian children had EED. Additional children will be enrolled to account for children who drop out or are excluded during the course of the study, as well as for some children who will not have a satisfactory data collection due to technical issues with the urine collection. The differences in lactulose recovery before and after the intervention will be calculated and compared between the intervention and control groups using *t* tests if the data are normally distributed or the non-parametric Wilcoxon Rank Sum Test if the data are not normally distributed.

Secondary outcomes of interest include linear and ponderal growth, adverse gastrointestinal symptoms, and any side effects due to the interventions. Linear growth will be calculated as the change in length over time, expressed as mm/day. Weight change will be calculated as the change in weight over time, normalized to the enrollment weight, and expressed as g/kg/day. Exploratory analyses of mRNA markers of intestinal inflammation found in the stool will also be conducted as part of our ongoing investigations into identifying novel biomarkers for EED [43, 44].

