**Methods/design:**

A prospective randomized placebo-controlled parallel-group randomized controlled trial will be conducted to determine if a daily supplement of lactoferrin and lysozyme, two important proteins found in breast milk, can decrease the burden of EED and stunting in rural Malawian children aged 12–23 months old. The intervention and control groups will have a sample size of 86 subjects each. All field and laboratory researchers will be blinded to the assigned intervention group, as will the subjects and their caregivers. The percentage of ingested lactulose excreted in the urine (Δ%L) after 4 h will be used as the biomarker for EED and linear growth as the measure of chronic malnutrition (stunting). The primary outcomes of interest will be change in Δ%L from baseline to 8 weeks and to 16 weeks. Intention-to-treat analyses will be used.

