Children will be asked to take no food (water and breast milk are permitted) after 10 pm on the evening before each sample collection date (weeks 0, 8, and 16). Each child will meet at the community meeting point in the village at 6 am with the research team. Each child then will drink 20 mL of a solution containing 5 g lactulose. Children who spit up or vomit the solution will return on a subsequent day to try again. Adhesive urine bags will then be placed on the child’s perineum to capture each urination. Once a child has voided any quantity of urine, the bag will be removed and the urine will be transferred to a clean container specific to the child, and then a new urine bag will be placed on the child. Thimerosol (10 mg) dissolved in 20 μL of water will be added to each child’s urine container to prevent bacterial degradation of the sugars. Caretakers and children are told to avoid breastfeeding, and will remain at the community meeting point for the next 4 h. Four hours after drinking the sugar solution, children will be encouraged to void and complete the urine collection, after which the total volume of urine will be quantified and aliquots portioned into cryovials. These samples will be stored in liquid nitrogen tanks in the field and then stored in –80 °C freezers until they can be transported back to the United States. The urinary concentration of lactulose will be measured by high-pressure liquid chromatography (HPLC) as described previously [62]. The total excretion of lactulose will be determined by multiplying this concentration by the total volume of urine.

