### Data management and analysis

Clinical data focusing on demographic and anthropometric values will be collected on standardized forms by field workers. Data will be double-entered into a password-protected Microsoft Access database by research assistants blinded to the intervention assignment. All discrepancies will be resolved by examination of the original forms and discussion with the relevant field workers. After entering all data and resolving inconsistencies, the data set will be locked. For anthropometric values, comparisons will be made between the lactoferrin-lysozyme mixture and the control rice flour groups. Fisher’s exact test will generally be used to compare discrete parameters, and Student’s *t* test will be used for continuous parameters. A difference with *P* < 0.05 will be considered statistically significant. These statistical methods will also be used for all clinical data and EED measures.

All trial data, including personal information, will be kept in password-protected encrypted computer databases on password-protected computers. Paper records will be kept in locked file cabinets and the research team’s headquarters in locked buildings. Given the relatively short duration of the study and the need to analyze all urine concentrations simultaneously at the end of the study, no interim analyses are planned and no stopping guidelines have been established. The full protocol, participant-level dataset, and details of all statistical analyses will be made available to any interested parties after the conclusion of the trial by contacting the principal investigators.

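### The primary test compares raw before-after differences in lactulose excretion and makes no adjustment for the week 0 value; this is unbiased but gives away precision

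*Protocol article*

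**What the plan says.** The abstract names two primary time points: "The primary outcomes of interest will be change in Δ%L from baseline to 8 weeks and to 16 weeks". The primary test is fixed in Outcomes and sample size: "The differences in lactulose recovery before and after the intervention will be calculated and compared between the intervention and control groups", using a t test for normal data and a Wilcoxon rank sum test otherwise. Data management and analysis names only Fisher's exact test and Student's t test, then adds: "These statistical methods will also be used for all clinical data and EED measures". No model with a baseline covariate appears anywhere in the article.

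The baseline value is there to be used. Under Lactulose absorption test, children fast from "on the evening before each sample collection date (weeks 0, 8, and 16", so the same measurement is planned before treatment and at both follow-ups.

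The sizing statement plans for 86 children per arm. It explains that number by the effect sought: "This sample size was chosen to detect a decrease of 0.05% in Δ%L between the two groups". The error rates attached to it are a 5% alpha and 90% power. On variability the article says only: "This assumes that urinary lactulose measurements will be distributed similarly to prior studies". It gives no SD and no correlation.

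**The concern.** This is a choice that the article states, not a detail left to an unseen analysis plan. A two-sample test on differences subtracts the whole baseline value, which amounts to fixing the regression slope on baseline at 1. When two readings on the same child are imperfectly correlated, the best slope is below 1, and subtracting the full baseline adds baseline noise to the outcome. Such noise is plausible here: urine is bag-collected over 4 hours, excretion is a concentration multiplied by a total volume, and the article itself expects some collections to fail.

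At stake is the width of the confidence interval for the primary effect and the chance of detecting the target difference of 0.05. The trial would pay for precision that it already has in hand.

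**Working it through.** **Inputs from the article.** n = 86 per arm, difference 0.05 percentage points, alpha 5%, power 90%, 1:1 allocation. **Assumptions.** Two-sided alpha (sidedness is not stated), equal variance at baseline and follow-up, and ρ shown over a range because the article gives none.

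**Step 1: the plan's own figure.** Without an SD, 86 cannot be reproduced independently; the SD can only be back-solved:

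SD = 0.05 / [√(2/86) × (1.960 + 1.2816)] = 0.05 / (0.1525 × 3.2415) = 0.101.

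The noncentral t gives 0.1006. A round SD of 0.10 would give 85 per arm, so the design is coherent with an SD near 0.10. The arithmetic does not show whether that SD belongs to one measurement or to a change.

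**Step 2: variance.** Let s be the single-visit SD and b the slope applied to baseline. Per child,

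Var(follow-up − b × baseline) = s²(1 + b² − 2bρ).

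- Change score, b = 1: 2s²(1 − ρ).
- Baseline-adjusted, b = ρ (the minimum): s²(1 − ρ²).
- Ratio, adjusted to change score: (1 + ρ)/2, which is 0.60 at ρ = 0.2, 0.65 at 0.3, 0.75 at 0.5 and 0.85 at 0.7.

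**Step 3: power at 86 per arm (normal theory).** By Step 1, a test whose SD is 0.101 has a standardised signal of 3.2415.

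*Reading A: 0.101 is the single-visit SD.*

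- Change score: power = Φ(3.2415/√(2(1−ρ)) − 1.96). At ρ = 0.3: Φ(2.740 − 1.96) = 78%.
- Adjusted: power = Φ(3.2415/√(1−ρ²) − 1.96). At ρ = 0.3: Φ(3.398 − 1.96) = 92%.

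*Reading B: 0.101 is already the SD of the change.*

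- Change score: 90% by construction.
- Adjusted: power = Φ(3.2415/√((1+ρ)/2) − 1.96). At ρ = 0.5: Φ(3.743 − 1.96) = 96%.

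| ρ | A: change score | A: adjusted | B: change score | B: adjusted |
|---|---|---|---|---|
| 0.2 | 73% | 91% | 90% | 99% |
| 0.3 | 78% | 92% | 90% | 98% |
| 0.5 | 90% | 96% | 90% | 96% |
| 0.7 | 99% | 99.5% | 90% | 94% |

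The noncentral t gives the same figures to this rounding.

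**Step 4: the Wilcoxon branch.** The figures above are for the t test. For skewed data, lognormal excretion was simulated with a single-visit SD of 0.101 at 86 per arm; the distribution is an assumption. With a coefficient of variation of 1.0, ρ = 0.2 and an additive effect, a linear model on untransformed values had about 91% power against about 97% for the planned Wilcoxon test on differences. A rank-based model adjusted for baseline did at least as well as both planned tests in every scenario run.

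**The case against.** The strongest reply is that nothing here is invalid. Under 1:1 randomisation the change-score comparison is unbiased, and chance baseline imbalance is variation that the test already counts in its standard error. That stands: the point is about efficiency only.

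A second reply is that the 90% may be correct as printed. The target is stated as a difference in Δ%L, and if the planners used the SD of the change, there is no shortfall. The article's wording about measurements leans towards a single-visit SD, but Δ%L is used both for the level and for the outcome whose change is studied, so neither reading can be proved.

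A third reply also stands: where data are skewed, a linear model on raw values can lose to the planned Wilcoxon test (Step 4). The remedy must therefore carry its own provision for skewness.

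A reader might go on to infer four stronger things, which the article does not support:

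- *The trial is underpowered.* That follows only under Reading A with ρ below 0.5.
- *Leaving ρ unstated is itself a fault.* A journal article commonly leaves such inputs to the full protocol, and this one says that a full protocol exists.
- *Separate tests for each visit throw away a child's other visit.* They do not. A failed week 8 collection leaves the week 0 to 16 difference intact, and the reverse holds too. Only a failed baseline removes both.
- *Adjustment secures the power whatever the SD.* If the true SD is larger than 0.101, the adjusted analysis loses power as well.

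**Conclusion.** The point holds as a loss of precision from a stated analysis choice. The direction is firm: in large samples the variance with a fitted baseline slope cannot exceed that with the slope fixed at 1. The size is not firm. The ratio (1+ρ)/2 needs equal variances at the two visits, and both the SD and ρ are missing from the article. For ρ between 0.2 and 0.7 the variance reduction is 40% down to 15%. In power, the gain is 18 percentage points at ρ = 0.2 and 6 at ρ = 0.5 under Reading A, or from 90% to 94–99% under Reading B. These figures assume two-sided alpha and roughly normal data. For skewed data, the advantage over the planned Wilcoxon test depends on modelling excretion on a suitable scale.

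The change is worth making, but the planned analysis would not give a wrong answer without it.

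**What to change.** For each primary time point, week 8 and week 16, estimate the treatment difference in the percentage of lactulose excreted from a model with the week 0 percentage as covariate. This can be two separate models, or one mixed model with baseline, visit, treatment and treatment-by-visit. Keep both time points primary; reporting week 16 alone would change the outcome structure that the article sets.

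For skewed data, specify in advance a log-transformed or rank-based version that also adjusts for baseline, in place of the Wilcoxon test on differences. Keep the change-score comparison as a sensitivity analysis. Use %L for the level and reserve Δ%L for the change.

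The cost is small: no new data, visits or children, and a little more analysis work. The one real constraint is that the scale for skewed data must be chosen before the urine results are seen. That should still be feasible, since the article describes recruitment as ongoing, plans no interim analysis, and will assay all urine together at the end.

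### The primary test on before-after lactulose differences uses only children with both collections valid; one longitudinal model of weeks 0, 8 and 16 would be more precise at almost no cost

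*Protocol article*

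**What the plan says.** The Abstract (Methods/design) names two primary changes: "The primary outcomes of interest will be change in Δ%L from baseline to 8 weeks and to 16 weeks". It adds: "Intention-to-treat analyses will be used".

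The section Outcomes and sample size fixes the analysis variable and the test. On the variable it says: "The differences in lactulose recovery before and after the intervention will be calculated and compared between the intervention and control groups". The choice of test depends on the distribution: a t test under normality, a Wilcoxon rank sum test otherwise. The same section foresees drop-out, exclusions and "some children who will not have a satisfactory data collection due to technical issues with the urine collection", and provides for them by enrolling more children.

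Other sections bear on the point:

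- **Lactulose absorption test:** collections are at weeks 0, 8 and 16. A repeat is stated only for a child who does not keep the test solution down, not for a failed urine bag.
- **Eligibility criteria:** children who cannot provide the required samples are excluded.
- **Study participation:** the study number is given before the baseline test, and the supplement is handed out after baseline sampling.
- **Randomization and blinding:** the study number determines the arm, and 125 numbers are prepared for each arm.
- **Anthropometry:** children found acutely malnourished at a later visit are excluded from the study.

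**The concern.** A two-sample test on differences has no place for a child with only one of the two values. Three kinds of child are affected:

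- A child with an unusable week 0 result but valid later results enters neither primary comparison.
- A child with valid week 0 and week 8 results but none at week 16 enters only the week 8 comparison. The week 8 result does nothing for the week 16 estimate.
- The reverse holds for a child who lacks only week 8.

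Separately, an unadjusted difference is a less precise use of the baseline than adjustment for it, unless the correlation between visits is close to 1. Precision is what is clearly at stake. Urine collection in this age group is laborious, and results already paid for would be left out or used inefficiently. Extra enrolment restores the number of pairs but does not recover those results.

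**Working it through.** **The plan's own figure.** Inputs: "This sample size was chosen to detect a decrease of 0.05% in Δ%L between the two groups" "with an alpha value of 5% and 90% power", with 86 per arm. No standard deviation is given, only that "This assumes that urinary lactulose measurements will be distributed similarly to prior studies". So 86 cannot be reproduced independently, but it can be inverted. With n = 2(1.960 + 1.282)² SD²/0.05², two-sided, 86 per arm implies SD = 0.05 × √(86/(2 × 10.51)) = 0.101 for the change. This value is used below only for power.

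**Assumed inputs (not in the document).** Each collection fails independently with probability f = 5-15%. A further 0-10% (d) leave between weeks 8 and 16. Variance σ² is equal at each visit, and the correlation ρ between any two visits is 0.2-0.5.

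**Formulas for the week 16 contrast, n randomised per arm, p = share with a valid week 0/week 16 pair:**

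- Unadjusted difference, as planned: variance = 4(1 − ρ)σ²/(np).
- Complete pairs adjusted for baseline: variance = 2(1 − ρ²)σ²/(np).
- Longitudinal model with a common baseline mean: variance from the expected information summed over all patterns of missing visits.

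The ratio of the second to the first is (1 + ρ)/2. Baseline adjustment alone therefore lowers the variance by (1 − ρ)/2, which is 40% at ρ = 0.2 and 25% at ρ = 0.5.

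**Worked example, ρ = 0.3, f = 10%, d = 10% (variances in units of σ²/n):**

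| | Baseline fails as often as follow-up | No baseline failures |
|---|---|---|
| p | 0.9 × 0.9 × 0.9 = 0.729 | 0.9 × 0.9 = 0.81 |
| Unadjusted difference | 4 × 0.7/0.729 = 3.84 | 4 × 0.7/0.81 = 3.46 |
| Adjusted complete pairs | 2 × 0.91/0.729 = 2.50 | 2 × 0.91/0.81 = 2.25 |
| Longitudinal model | 2.25 | 2.23 |
| Reduction against adjusted pairs | 10% | 0.9% |
| Reduction against planned test | 42% | 36% |

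**Whole range of assumptions:**

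| | Baseline fails as often as follow-up | No baseline failures |
|---|---|---|
| Gain from partial data, against adjusted pairs | 4-15% | 0.1-2.2% |
| Total gain, against planned test | 28-49% | 25-40% |

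As equivalent children, a 15% lower variance is worth 1/0.85 − 1 = 18% more, and a 2.2% lower variance about 2% more. Almost all the partial-data gain comes from children without a valid baseline. Borrowing from week 8 to inform week 16 adds little.

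**Power of the planned test.** If all 125 numbers per arm are used, 1 − 86/125 = 31% may be lost before fewer than 86 pairs remain. Without drop-out this allows up to about 17% failure per collection, since √(86/125) = 0.83. At 10% failure, 125 × 0.81 = 101 pairs remain and power is 94%. The worst corner of the range (15% failure at each visit, 10% drop-out) leaves 125 × 0.650 = 81 pairs. At 80 pairs power is 87.8%.

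**The case against.** The strongest objection concerns baseline failures. A child who cannot give the samples is ineligible, and the supplement follows baseline sampling, so many failed week 0 bags may never reach the treated population. That largely stands, and it is why the lower range of 0-2% has to be shown beside 4-15%. The screen is not complete. The study number, and with it the arm, precedes the test, and all urine is assayed together at the end of the study, so a baseline can prove unusable after treatment. The document does not show where between the two ranges the truth lies.

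A reader might infer more than the text supports:

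- **That the analysis contradicts intention to treat, or is biased.** Neither is shown. The claim is one sentence in the Abstract and is compatible with analysis by assigned arm. The article attributes unsatisfactory collections to technical causes, which gives no reason to expect a difference by arm or outcome. The malnutrition exclusions at later visits are a plausible route to bias, but only a possible one.
- **That one failed bag removes a child altogether.** Only a missing baseline does that.
- **That the trial is underpowered.** The 125 numbers per arm cover nearly all the loss scenarios, although they are a capacity and not a promised enrolment.
- **That imputation is ruled out.** The article names none, but a full plan could add it. Separate testing at each visit is likewise inferred from two primary changes and two-sample tests.

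It is also true that comparing change between randomised arms is a valid analysis. The case for replacing it is efficiency.

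**Conclusion.** The point holds as a matter of precision. The article itself fixes the variable and the test, so this is not a detail left to an analysis plan: as written, each comparison can use only children with both collections valid.

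The partial-data share of the gain is modest and uncertain, because it depends on how many baselines fail after allocation. The larger gain, about 25-49% of the week 16 variance in total, comes mainly from replacing the unadjusted difference with an analysis that adjusts for baseline.

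These sizes rest on assumed failure, drop-out and correlation, equal variances and independent failures. They are measured against the t test; the Wilcoxon alternative was not evaluated. Higher correlation shrinks the gain: at ρ = 0.7 baseline adjustment alone gives (1 − 0.7)/2 = 15%. This is an inexpensive improvement worth making, not a flaw that invalidates the trial.

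**What to change.** Make the primary analysis one longitudinal model of all valid lactulose results at weeks 0, 8 and 16, with a common baseline mean for the two arms (justified by randomisation), arm-by-visit terms at weeks 8 and 16, and an unstructured within-child covariance. Read the arm differences at both visits from this model. Every randomised child with at least one valid result then contributes, including results obtained before a child leaves the study.

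Keep the absolute percentage-point scale, on which the 0.05% difference is powered. If a log scale is chosen because of skewness, say beforehand that the effect becomes a ratio and no longer matches that difference. Report the complete-pair comparison, by t test or Wilcoxon test, as a sensitivity analysis.

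The cost is analysis wording and standard mixed-model software, with no extra children or samples. Because the urine is assayed together at the end and no interim analysis is planned, the change can be fixed before lactulose results exist. The small downside is reliance on a model that treats missing results as missing at random given those observed. State this assumption; the model does not cure losses that depend on unobserved values.
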